### Participant timeline {13}

The study will take approximately 1.5 years to completion. The screening period is scheduled after a minimum of 7 days and a maximum of 14 days during inpatient rehabilitation. Once the participant enters the study and is randomized, the treatment period lasts for 6 months with biweekly follow-up for SAEs/AEs and device deficiencies. Any participant who is not responding to the visit emails will be followed up with 3 times until being considered lost to follow up. Figure 2 displays the study schedule in detail.

**Fig. 2 Fig2:**
[figure not shown]
The study schedule in detail

### Sample size {14}

In total, 104 participants are expected to be recruited, 52 for the intervention group and 52 for the control group each. The sample size calculation is based on the primary outcome, the difference between groups in the average steps per day within 1 week at the 6-month follow-up. As this study had no pilot study, there are no further statistical sample size considerations. The well-established minimally important difference in steps per day after pulmonary rehabilitation lies between 600 and 1100 steps as measured with an activity tracker during an intervention. Assuming a standard deviation of the outcome variable of 2500 steps/day, an expected effect size of 2000 steps/day can be assumed for programs combining physical activity counseling with PR to increase activity, according to current meta-analyses. To achieve 80% power and a significance level of 5% (one-sided), a sample size of 26 patients in each group is required, which results in a total sample size of 104, assuming a drop-out rate of 50%. The sample calculation is based on a one-tailed nonpaired *t* test comparing the two groups with each other at the final visit at the end of the follow-up period.

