### Implementation {16c}

Randomization will be performed on the patient level with a 1:1 ratio using block randomization with varying block sizes, stratified per study center. Once the random number is delivered to the study site, it is the duty of the site personal to implement the procedures as specified in the protocol.

The study nurse will carry out a short training program (20 min) to demonstrate the use of the wearable and mobile device platform (smartphone) for both groups. Additionally, the following steps will be taken to explain the group assignment to the subjects.

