### Statistical methods for primary and secondary outcomes {20a}

#### Primary analysis

Baseline characteristics of the study participants will be summarized according to numbers and percentages for qualitative variables, means, and standard deviations for quantitative variables with normal distributions and medians and 25th–75th percentiles for quantitative variables with nonnormal distributions. Differences in the change in the primary outcome from baseline to the 6-month follow-up between the intervention and control group participants will be compared by linear regression analyses corrected for relevant confounders and baseline values. The same analysis will be used for continuous secondary outcomes. The primary analysis will be done with a one-sided nonpaired *t* test comparing the two groups with each other at the final visit at the end of the follow-up period.

For the main analyses, we will compare the control group with the intervention group using an intention-to-treat approach. This study is designed as a superiority study.

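### The stated inputs (2000 steps/day, SD 2500, one-sided 5%, 80% power) need 21 per group, not 26; with 26 the declared test has about 88.5% power

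*Protocol article*

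**What the plan says.** Sample size {14} prints every input to the calculation. On variability: "Assuming a standard deviation of the outcome variable of 2500 steps/day". On the difference: "an expected effect size of 2000 steps/day can be assumed". On the result: "To achieve 80% power and a significance level of 5% (one-sided), a sample size of 26 patients in each group is required". The test is named next: "The sample calculation is based on a one-tailed nonpaired" t test, comparing the groups at the final visit. The 26 per group is raised to 52 per group, 104 in total, for a 50% drop-out rate. Implementation {16c} gives the allocation: "Randomization will be performed on the patient level with a 1:1 ratio".

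The Primary analysis section under {20a} declares the same test: "The primary analysis will be done with a one-sided nonpaired" t test at the end of follow-up, in a trial described as a superiority study. One-sidedness is therefore stated consistently, twice in the sample size section and once in the analysis section. No reason for it is given in either place.

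**The concern.** A standardised difference of 0.8 is large, and 26 per group is the familiar answer for a two-sided 5% t test at that effect size. A one-sided test at the same nominal 5% has a lower critical value and needs fewer patients. If 26 really is the requirement, the level is not one-sided 5%. If the level is one-sided 5%, then either 26 or 80% is wrong.

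The mismatch touches the error rate of the confirmatory test. The declared rule allows a 5% chance of a false conclusion in favour of the app, while the planned sample already meets the 80% power target at 2.5% in that tail. A reader of the final report could not tell which rule the trial was designed around. In an open-label trial whose sponsor supplies the app, sidedness that is unsettled until the data are in would be hard to defend.

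**Working it through.** **Inputs.** Difference 2000 and SD 2500 steps/day, so d = 2000/2500 = 0.80; level 5% one-sided; target power 80%; unpaired t test; drop-out 50% (all from Sample size {14}). Allocation 1:1 (Implementation {16c}).

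**Formula.** With n analysed per group, the t statistic under the alternative follows a noncentral t distribution with 2n − 2 degrees of freedom and noncentrality d√(n/2). Power is the probability that it exceeds the critical value of the central t distribution at the chosen level. The two-sided test adds the lower tail, which is negligible here.

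**Step 1: the plan's own figure at its stated level (one-sided 5%).**
- n = 20: noncentrality 0.8 × √10 = 2.53; power 79.9%.
- n = 21: noncentrality 0.8 × √10.5 = 2.59; power 81.7%.

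The requirement is 21 per group, so 26 is not reproduced. The normal approximation, 2(1.645 + 0.842)²/0.8² = 19.3, rounds up to 20 and lies further from 26. The gap of 5 to 6 per group is not rounding.

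**Step 2: the same inputs at two-sided 5% (one-sided 2.5%).**
- n = 25: noncentrality 0.8 × √12.5 = 2.83; power 79.1%.
- n = 26: noncentrality 0.8 × √13 = 2.88; power 80.7%.

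The requirement is exactly 26. The normal approximation gives 2(1.960 + 0.842)²/0.8² = 24.5, rounded up to 25.

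**Step 3: power of the declared test at the declared size.** One-sided 5% with n = 26 gives 88.5% (89.2% by normal approximation), about 8 points above the stated 80%.

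**Step 4: drop-out.** 26/(1 − 0.5) = 52 per group, 104 in total, which reproduces the plan. Starting from 21: 21/(1 − 0.5) = 42 per group, 84 in total, 20 fewer than planned. The drop-out step is right, so the discrepancy arises before it.

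| Level | n per group for 80% power | Randomised at 50% drop-out | Power at n = 26 |
|---|---|---|---|
| One-sided 5% (as declared) | 21 | 84 | 88.5% |
| Two-sided 5% (one-sided 2.5%) | 26 | 104 | 80.7% |

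**Step 5: what sidedness does to the decision.** With 26 analysed per group and SD 2500, the standard error of the difference is 2500 × √(2/26) = 693 steps/day. The smallest significant difference is 1.676 × 693 = 1162 steps/day one-sided and 2.009 × 693 = 1393 two-sided. An observed difference between these two would succeed under the declared rule but not under two-sided 5%.

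**The case against.** Nobody can fairly say that this error leaves the trial short of patients. A reader who sees that the stated power is wrong might infer an underpowered trial, but the error runs the other way: on the plan's own assumptions 26 per group exceeds the 80% target under the declared test. That stands in full. The immediate consequence is a power figure that is too low, or up to 20 patients more than the stated target needs.

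The one-sided choice is also prespecified and consistent. The document does not contradict itself on sidedness, and a one-sided 5% test is not invalid in itself. Preferring 2.5% in the upper tail is a design recommendation that goes beyond the arithmetic. This stands too, though the choice still lacks a stated reason.

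Three further readings are tempting but not supported:

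- That the calculation was certainly two-sided and then mislabelled. The exact match makes this the likeliest explanation, but the article does not say how 26 was obtained. What is shown is only that 26 does not follow from the stated inputs.
- That the larger upper-tail error buys nothing. It buys about 8 points of power (88.5% against 80.7%). It is unnecessary only for reaching the 80% target.
- That a result against the app could not be reported. The one-sided test cannot declare such a difference significant, but the estimate can still be given. The Primary analysis section also plans a regression on change whose sidedness is not stated, and the Safety analysis uses a two-tailed test.

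Finally, the thresholds in step 5 are conditional. The plan substitutes baseline or last known values for missing final data under intention to treat, so up to 52 per group may enter the test. With 52 per group and an unchanged SD, the standard error is 2500 × √(2/52) = 490, and the thresholds fall to about 814 and 972 steps/day. Whether the SD and the effect would be unchanged under such substitution is a separate question.

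**Conclusion.** The point holds as an inconsistency between size, level and power. On the stated difference, SD and test, one-sided 5% with 80% power requires 21 per group (84 in total), while 26 per group gives about 88.5%. The printed requirement is therefore wrong as written, by 5 patients per group or by about 8 points of power, in the safe direction. That 26 is exactly the two-sided 5% requirement is strong circumstantial evidence about its origin and no more.

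The power figures assume normally distributed outcomes with a common SD of 2500, a true difference of 2000 steps/day and the stated number analysed per group. The thresholds of 1162 and 1393 steps/day hold only with 26 analysed per group and that SD. None of the arithmetic needs an input from outside the article, so a separate analysis plan could change the declared test but could not make the present sentence correct.

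**What to change.** Make sidedness, size and power agree in Sample size {14} and in the Primary analysis section before any analysis.

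**Preferred.** Declare the primary t test two-sided at 5% (equivalently one-sided 2.5%), keep 26 evaluable per group and 104 randomised, and state the power as about 81% for 2000 steps/day with SD 2500. This meets the 80% target with half the upper-tail error. It needs no extra patients or procedures. It gives up about 8 points of power compared with one-sided 5%. It is also more than an edit of wording: recruitment began in August 2019, and the section on deviations from the statistical plan requires a report to the ethics committee before implementation, with a possible protocol amendment. If the change counts as substantial, section {25} adds ethics approval and an entry in the trial register.

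**Minimal alternative.** Keep one-sided 5%, give the reason for it, and restate the power as about 88% with 26 evaluable per group, or restate the requirement as 21 per group (84 in total at 50% drop-out). Keeping 26 and correcting the power leaves the test itself unchanged and costs only the correction and the justification.

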### Handling of missing data and drop-outs

As described above, the main analyses will be conducted with an intention-to-treat approach, and missing follow-up data for patients who do not complete the V8 assessments will be substituted with baseline assessment data or the last known data (i.e., last outcome carried forward).

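### The stated 80% power is for 26 completers per group, not for the planned intention-to-treat test on 52 per group with substituted values, and 26 matches a two-sided rather than the stated one-sided 5%

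*Protocol article*

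**What the plan says.** All statements are in the protocol article.

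- **Sample size {14}:** "Assuming a standard deviation of the outcome variable of 2500 steps/day" and "an expected effect size of 2000 steps/day can be assumed". From these: "To achieve 80% power and a significance level of 5% (one-sided), a sample size of 26 patients in each group is required". The total follows as "a total sample size of 104, assuming a drop-out rate of 50" per cent, that is 52 per group. The section names a one-tailed unpaired t test at the final visit.
- **Primary analysis:** the same one-sided unpaired t test at the final visit is labelled the primary analysis, and for the main analyses "we will compare the control group with the intervention group using an intention-to-treat approach". The same paragraph also describes a linear regression on change, adjusted for confounders and baseline values.
- **Handling of missing data and drop-outs:** "missing follow-up data for patients who do not complete the V8 assessments will be substituted with baseline assessment data or the last known data".
- **Methods to handle protocol nonadherence and missing data {20c}:** this second statement of the rule names only the last available measurement and does not mention baseline.

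**The concern.** Going from 26 to 52 per group is the right step if half the patients vanish from the analysis and the other half show the full 2000-step difference. The primary analysis is set up otherwise. Drop-outs stay in, each with a value from before the end of treatment, possibly from before it began. That doubles the number of values tested but can shrink the expected difference between groups. The sample size section allows for neither.

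With half of each arm expected to drop out, the handling of drop-outs largely determines the power. A single figure of 80% hides this. If the trial ends without a significant difference, readers will need to know whether dilution by substituted values could explain it, and the present power statement does not help them.

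**Working it through.** **Inputs.** From Sample size {14}: difference 2000 steps/day, SD 2500, one-sided 5%, power 80%, 26 per group, 50% drop-out, 104 in total. From the analysis sections: unpaired t test at the final visit, all randomised, missing values substituted. Not in the document, so assumed: the share f of the 2000-step effect present in a substituted value. Also assumed: equal drop-out in both arms, drop-outs comparable with completers, and SD 2500 for substituted as well as observed values.

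**Step 1: reproduce the plan's figure.** By the normal approximation, n per group = 2 × (z for alpha + z for power)² × (SD/difference)².

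- One-sided 5%: 2 × (1.645 + 0.842)² × 1.25² = 19.3, so 20. The exact t test needs 21.
- Two-sided 5%: 2 × (1.960 + 0.842)² × 1.25² = 24.5, so 25. The exact t test needs 26.

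So 26 is reproduced, but as the two-sided t-test number. With 26 per group the noncentrality is 2000 / (2500 × √(2/26)) = 2.88, which gives power of 88.5% one-sided and 80.7% two-sided. The inflation itself is correct: 26 / (1 − 0.5) = 52 per group, 104 in total.

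**Step 2: power of the planned test, 52 per group, 50% drop-out.**

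- Expected difference = 2000 × (0.5 + 0.5f).
- The intervention arm mixes completers and drop-outs with different means, so its variance is 2500² + 0.25 × (2000 × (1 − f))². The control variance is 2500². The pooled SD is the root of their average.
- Noncentrality = difference / (pooled SD × √(2/52)). For f = 0 this is 1000 / (2598 × 0.196) = 1.96.

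| Effect retained in substituted values | Expected difference | Pooled SD | Power, one-sided 5% |
|---|---|---|---|
| 0% (pure baseline substitution) | 1000 | 2598 | 62% |
| 25% | 1250 | 2556 | 80% |
| 50% | 1500 | 2525 | 91% |
| 100% | 2000 | 2500 | 99% |

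Simulation of the first row also gives 62%. The break-even for 80% lies at about a quarter of the effect.

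**Step 3: vary the drop-out rate, pure baseline substitution.** With drop-out rate d, the difference is 2000 × (1 − d) and the added intervention-arm variance is d(1 − d) × 2000². One-sided power is 94% at d = 20%, 86% at 30%, 76% at 40% and 62% at 50%.

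**Step 4: the other analysis named in the protocol.** The worst case of step 2 (50% drop-out, every missing value set to baseline) was simulated with adjustment for baseline and SD 2500 at both times. One-sided power is about 81%, 89% and 97% for baseline-to-follow-up correlations of 0.3, 0.5 and 0.7. These correlations are assumed; the document gives none.

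**The case against.** The strongest reply is that 62% is an extreme case. The rule also allows the last known value, and {20c} names only that. Steps are recorded daily and passively, patients who stop early are asked to complete the follow-up assessments at termination, and follow-up after withdrawal continues where the patient agrees. A last known step count would carry no effect only for someone with no data after randomisation, or none by which the app had begun to work. If half the effect is carried, one-sided power is 91%. The 50% drop-out rate is also a planning allowance: at 30%, even pure baseline substitution leaves 86%. With baseline adjustment the one-sided shortfall disappears over the correlations tried.

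All of this stands, and it limits the point. A reader might infer that the trial's real power is 62%, or that an app worth 2000 steps would be missed in more than a third of such trials. The document does not support that: it holds only if 50% drop out and every substituted value carries no effect. Nor should a two-sided figure (49% in that worst case) be set against the stated 80% as the plan's power, since the planned test is one-sided. Like for like, the worst-case fall is from 88.5% to 62% one-sided, or from 80.7% to 49% two-sided.

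The reply does not remove the mismatch. Both versions of the missing-data rule keep drop-outs in, the final-visit t test is the analysis labelled primary, and nothing in the sample size section supports 80% for it.

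**Conclusion.** The point holds as a mismatch between the power statement and the analysis, not as proof that the trial is underpowered. At the planned 50% drop-out, one-sided power of the primary t test runs from 62% to 99%, depending on a retained effect that the protocol does not state. It is below 80% only if less than about a quarter of the effect is retained. The true figure may therefore be worse or considerably better than stated. The range rests on SD 2500 throughout, equal drop-out in both arms and comparable drop-outs.

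The sidedness error depends on none of these assumptions. At the stated one-sided 5%, 26 per group gives 88.5%, and 21 would suffice for 80%.

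**What to change.** In Sample size {14}, restate the power for the analysis that will be run:

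- Name the population (all randomised), the drop-out rate and the expected difference with drop-outs included.
- Reconcile the two missing-data statements into one substitution rule, and quote power under that rule.
- Give power as a range over the retained effect, with 62% one-sided as the worst case rather than as the plan's single figure.
- Correct the sidedness: state either that 26 per group gives 88.5% at one-sided 5%, or that it was derived for a two-sided 5% test.
- If the baseline-adjusted regression is made primary, quote power for that model with the assumed baseline-to-follow-up correlation.

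The cost is a rewritten paragraph and a wider or less favourable power statement. The sample size need not change.

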### Recruitment {15}

The expected rate of recruitment from the centers is 2–3 patients per week. In case the trend does not follow with the theoretical recruitment rate, an additional site in either of the countries (Germany or Switzerland) could be considered.

Assignment of interventions: allocation

### Sequence generation {16a}

Randomization will be accomplished by using a software randomizer (https://www.randomizer.org).

### Concealment mechanism {16b}

For allocation concealment, the fabrication of lists will be done by the sponsor, and the allocation of each individual participant (using only ID, no personal data) will only be made available to investigators via email after reporting a patient being successfully included in the study to the sponsor. On the concluding day of the screening visit, if a patient is rendered eligible to participate in the study, the study staff will inform KAIA’s project management. After receiving the email, patients will be assigned to the corresponding group by the study center.

### Implementation {16c}

Randomization will be performed on the patient level with a 1:1 ratio using block randomization with varying block sizes, stratified per study center. Once the random number is delivered to the study site, it is the duty of the site personal to implement the procedures as specified in the protocol.

The study nurse will carry out a short training program (20 min) to demonstrate the use of the wearable and mobile device platform (smartphone) for both groups. Additionally, the following steps will be taken to explain the group assignment to the subjects.

#### Intervention group

Explanation of the 3 dimensions of the COPD app (exercise, education, relaxation)Starting of the COPD app and a training sessionSetting the individual goals for physical activity (steps per day).Synchronization of the smartphone

#### Control group

Setting the individual goals for physical activity (steps per day)Synchronization of the smartphone

### Assignment of interventions: open label study

#### Who will be blinded {17a}

Patients cannot be blinded due to the nature of the intervention. Blinding of statisticians or data managers will be carried out.

#### Procedure for unblinding if needed {17b}

The design is open label, so unblinding will not occur.

### Data collection and management

The investigators are responsible for ensuring the accuracy, completeness, and timelines of the reported data. All source documents will be completed in a neat, legible manner to ensure accurate interpretation of the data. Data reported in the eCRF derived from source data documents will be consistent with the source documents.

### Plans for assessment and collection of outcomes {18a}

Electronic data capture (EDC) will be used for this study. The study data will be transcribed by study-site personnel from the source documents into an electronic CRF and transmitted in a secure manner to the sponsor within the time agreed upon between the sponsor and the study site. The electronic file will be considered to be the eCRF. Olyro (www.olyro.de) will be used as the software to provide eCRFs and the database. eCRFs for each enrolled study participant will be filled in with all relevant data pertaining to the participant during the study.

Documented medical histories and narrative statements relative to the participants’ progress during the study will be maintained. These records will also include the following: originals or copies of laboratory and other medical test results (e.g., ECGs) which must be kept on file with the individual participant eCRFs. All data entered into the eCRF for the baseline visit, with the exception of clinical data, such as comorbidities, medication, and lung function measurements, which are taken from the electronic patient records in the clinics by the study nurses, will be source data and must also be available in the individual participant file either as print-outs or as notes taken by either the investigator or another responsible person assigned by the investigator.

Secondary outcomes (i.e., all patient-reported outcomes) will be reported by patients directly after sending a link to the patient that leads the patient directly to a webpage with the questionnaires mentioned above. Patient-reported outcomes will be collected via a web-based platform using individualized links sent to patients enrolled in the study and collected in the database. Personnel will not be given access to the system until they have been trained. Automatic validation procedures within the system check for data discrepancies during and after data entry and, by generating appropriate error messages, allow the data to be confirmed or corrected online by the designated investigator site staff. The investigator must certify that the data entered are complete and accurate.

Essential documents will be retained after the regular end or premature termination of the respective study according to the local regulatory requirements.

